### Qualitative substudy

The focus of our qualitative study will add value to the trial by:

1) Adding depth to the interpretation of the main findings of the trial;

2) Gaining new understanding over and above the quantitative trial findings by focusing on the process of the intervention from the perspectives of key stakeholders;

3) Exploring practice and policy issues relevant to implementation of the trial results.

Qualitative material will be collected from participants at two time points and from practitioners at one time point. The purpose is to capture participants’ experience of the intervention, which will be connected to their broader illness experience. We will address the impact of the interventions beyond reduction in pain, including influence on illness perception; health-related quality of life; and engagement in social activities and relationships.

Our methods involve the following:

1) We will conduct three focus group discussions with approximately eight participants (24 approximately in total) drawn from a general population with chronic neck pain. . These focus groups, which will involve people not involved in the trial, are designed to enable us to understand people’s initial perceptions about the social consequences of neck pain, the relative merits and initial perceptions of the interventions, and the potential of these interventions for implementation as referral options in primary care. These discussions with nonparticipants are valuable in their own right and will also generate valuable general themes, which we will be able to explore in more detail during individual interviews. We will advertise for participants.

2) We will conduct in-depth interviews with ten trial participants from each of the three arms. There will be two interviews for each patient, one toward the end of the intervention (approximately 40 to 60 minutes) and a second more focussed one at 12 months (approximately 20 to 30 minutes). The two interviews will capture the participants’ perceptions and experiences of their intervention, and the factors they associate with its impact over the short and longer term. The total interviews will number 60. Supplementary written qualitative material will also be sought from all remaining trial participants, by including an open question at the end of their 12-month questionnaire.

3) We will conduct three focus group discussions involving practitioners who are involved in the trial, one for acupuncturists, one for Alexander teachers, and one for general practitioners. These will be conducted during the intervention and follow-up phase of the trial, with approximately eight practitioners in each group. Our aim is to explore practitioner experiences and perspectives with a view to better understanding the implications if the interventions were implemented routinely in primary care.

Our approach to analysis will be iterative and aided by the use of Atlas.ti (version 5.2)software (Science Plus Group, Groningen, The Netherland, http://www.scienceplus.com). Initially, focus group discussions and interview material will be transcribed and organised according to analytical headings. During the analysis, regular meetings will be held between the research team to discuss the emergent themes from the fieldwork material. We will also be looking for potential points of comparison with the trial data. Focus group analysis will specifically concentrate on drawing out normative values and assumptions associated with trait identification. For the interviews, we will begin by identifying themes, which are first, interrogated in relation to each individual account, as a means of understanding a particular case; second, compared across cases by highlighting potential similarities and differences; and finally, related to those characteristics of the respondent that could be reasonably justified as an explanation which mediated experience. Our analysis will also benefit from any insights gained from the trial data and in particular look for ways of explaining some of the more quantitative findings. The meaning people give to the intervention, for example, will provide valuable material on how any intervention will work when faced with the ‘messiness’ of practice.

### Proposed sample size and a description of the power calculations

We will recruit 500 participants in total to the trial. Our sample size calculations were performed for a simple comparison of two groups. From our pilot, the standard deviation of the primary endpoint, the Northwick Park Questionnaire (NPQ), was 16%, and the correlation between baseline and 3-month NPQ was 0.69 [6]. A clinically meaningful difference on the NPQ is 5 percentage points [43], a 0.31 effect size. With 90% power and alpha = 5% we would require 113 participants per arm after adjusting for baseline. We are aiming for a loss to follow-up of 20% but in our estimate of sample size we are conservative, allowing for 30% loss to follow-up. Randomising into three equally sized groups, our required total sample size will be 500.

For our primary comparison, we will estimate the difference in mean score from the NPQ at 12 months between the acupuncture and control groups and between the Alexander Technique lessons and control groups, after adjustment for baseline pain score using analysis of covariance. Each of our two active interventions tested against control can be interpreted quite independently of the other. This does not constitute a problem of multiple testing, as there might be if we had two different kinds of acupuncture. If we find acupuncture to be significantly better than the control, then we would conclude that it worked. But this test would tell us nothing about Alexander Technique lessons versus control. Therefore when testing two independent hypotheses, we do not need to use multiple comparison procedures. We will, as a secondary analysis, estimate the clinical difference between acupuncture and Alexander Technique lessons.

### Planned recruitment methods

We will use our well-established ‘database’ recruitment method. We will recruit GP practices local to areas where there is sufficient capacity from acupuncturists and Alexander teachers. Potentially suitable participants will be identified from electronic medical records held by participating GP practices. This will involve searching for primary care consultations coded as related to neck pain, using pre-specified READ codes, and will be performed by practice staff. Only those patients who have consulted for neck pain three months or more before the database search will be invited to take part in the trial. Patients who have not consulted for neck pain, or have only done so for the first time within the preceding three-month period, will be excluded from the study. The lead GP within each practice will then be given the opportunity to exclude any unsuitable patients on the resulting list prior to information being sent to patients about the trial. General practices will then mail out patient information leaflets, baseline questionnaires and consent forms. The letter will ask patients if they still have problems with neck pain and if so, will invite them to complete the consent form and baseline questionnaire that includes the Northwick Park Questionnaire and to return these to the York Trials Unit. Questionnaires will be screened by the research team and a list compiled of all those who appear eligible to take part. This list will then be sent back to the lead GP for final approval, at which point the patient’s medical records will be examined in detail. Those who are subsequently approved will then be randomised using a secure method, and a letter sent to their GPs stating to which arm of the trial they have been allocated. Participants allocated to one of the active interventions will be sent a letter and invited to phone the office to arrange an initial appointment with a practitioner at a time and location that is suitable. A confirmation letter is then sent to the patient providing details of the appointment, and a logbook is sent to the practitioner.

In addition we will identify potential participants who respond to advertisements in GP practices. Patients interested in taking part in the study will be asked to phone the trial team on a free phone number for further information. If the patient is still interested in taking part, we will record the patient’s name, contact details and name of their GP practice on a secure database with restricted access, and send out a pack inviting them to join the study. This pack will include the participant information sheet, a baseline questionnaire, two consent forms (that is, the same documents sent to patients identified from the database search), a covering letter, and prepaid envelopes for return of completed consent form and questionnaire. Upon receipt, the questionnaire and consent form will be dealt with in the same way as those received from patients identified in a database search (see above).

In our neck pain pilot based in York we used this approach with one general practice with a list size of 15,694 patients, from which 227 had consulted with neck pain in the previous year [6]. Of these, 28 (12.3%) consenting patients were eligible to participate in the pilot and 24 (10.5%) were recruited. Since eligibility criteria are more restrictive in this trial (that is, minimum chronicity of three months) the proportion of volunteers deemed to be suitable at the point of secondary screening is likely to be less than that observed in the pilot study. However we are removing the cut-off of one year since previous consultation with neck pain, which in turn will support an increase in the number of volunteers per practice. We estimate a GP practice with a list size of 10,000 patients will identify 300 patients eligible for an invitation to participate in the trial. Of these, 5% are predicted to sign consent forms and be judged suitable when their baseline questionnaire is screened. We therefore expect to recruit on average 15 participants per practice from 33 general practices over a 12-month period.

### Attendance rates and loss to follow-up

Less than optimal attendance at sessions, as discussed above, is an inevitable part of a pragmatic trial given that our aim is to evaluate everyday practice. Early termination of an intervention can be a sign that it has worked, and that the neck pain is alleviated. Alternatively early discontinuation due to perceived lack of results may occur. To optimise attendance, practitioners will be selected for their training and experience, and will also receive induction into trial processes. Our experience with acupuncture trials is that 8 out of 10 sessions were taken up with our back pain trial [9] and 9 out of 10 sessions for irritable bowel syndrome [44]. Similar data were found from the Alexander Technique lessons for the back pain trial [13].

Loss to follow-up (of self-report questionnaire data) will be minimised by a number of means, including having the research team highly organised and efficient in handling all matters that affect participants. Questionnaires will be sent out in a timely manner along with text message reminders. Where a questionnaire is not returned, reminders will be sent out. If the reminders fail to get a response, a telephone call will be made (by a researcher blinded to group allocation) to collect the data for the primary outcome measure and the EQ-5D. In our experience of postal questionnaires with additional follow-up as described above in a trial of acupuncture for low back pain, we found response rates of over 93% in the acupuncture group and 83% in the usual care group at 12 months [9]. Similar response rates were found in the Alexander Technique lessons for back pain trial [13]. All participants will receive £5 with their final questionnaire, which is likely to encourage a higher return rate.

### A summary of the statistical analysis plan

Analysis will be by intention-to-treat. All of those randomly allocated will remain in their group for analytical purposes irrespective of whether or not they actually take up or fully adhere with the intervention. Statistically we will use analysis of covariance to control for baseline values. Multiple imputation will be used to account for missing values.

As this is a pragmatic trial, participants are offered, but may not receive a full course of sessions or lessons. Some may discontinue if they get better before the end of their course. Others may discontinue if they perceive no benefit. In a trial of Alexander Technique lessons for low back pain patients, average attendance was either 5 out of 6 offered lessons, or 20 out of 24 lessons offered [13]. We will incorporate Complier Average Causal Effect (CACE) analysis to control for any dilution effects of people not taking up their allocated intervention [45]. We will also ascertain whether there is a relationship between levels of attendance and outcome, and whether outcomes are better or not for those participants who have attended at least 75% of sessions.

To evaluate trajectories of change from the text message scores, we will fit a common curve for each group using polynomial regression. We will use a polynomial within-subject, by analysis of covariance, to enable us to plot an empirical curve for each group. We can compare the three groups statistically to test for interactions between intervention group and time. Moreover these text scores will provide useful data for multiple imputation for missing data.

We will use regression models to explore whether preference, belief or expectation are treatment effect modifiers. We will explore whether potential treatment effect mediators (self-efficacy, stress management, incorporation of advice about self-care and lifestyle) might be associated with longer term change.

We will investigate variations in outcomes between practitioners, which we call practitioner effects, in a separate analysis using the ‘artificial cluster’ method. Each control participant will hypothetically be allocated a practitioner, so that each practitioner is linked to a cluster of both intervention and control participants. For each practitioner the difference in mean NPQ score between those allocated to the intervention and those allocated control will be found and a confidence interval for the difference found by the t-method. Adjustment for baseline NPQ will be done using analysis of covariance on mean baseline NPQ for the cluster and using baseline minus outcome differences.

Outcome data will be examined to determine if it influences subsequent preferences by comparing participants’ pre-randomisation preferences to those given at 12 months post-randomisation.

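### The baseline adjustment stated for the exploratory practitioner analysis is inefficient and leaves practitioner estimates tied to chance baseline imbalance

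*Protocol article*

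**What the plan says.** The protocol article, under *A summary of the statistical analysis plan*, studies practitioner effects "in a separate analysis using the ‘artificial cluster’ method". Control participants are hypothetically assigned to practitioners, "so that each practitioner is linked to a cluster of both intervention and control participants". For each practitioner the article takes the difference in mean NPQ between the two sides, with "a confidence interval for the difference found by the t-method". On baseline it then says: "Adjustment for baseline NPQ will be done using analysis of covariance on mean baseline NPQ for the cluster and using baseline minus outcome differences".

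The main analysis in the same section is different: "Statistically we will use analysis of covariance to control for baseline values". The sample size section relies on that choice. It states that "the standard deviation of the primary endpoint, the Northwick Park Questionnaire (NPQ), was 16" percentage points and that "the correlation between baseline and 3-month NPQ was 0.69", and it reduces the required number per arm accordingly.

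Variation between practitioners is third in the list of matters to be explored under *Details of the trial*.

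**The concern.** The two named steps each fail to do what a baseline adjustment should do for a difference between two small groups.

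- **Cluster mean.** It is a single number for each practitioner, shared by both sides of that practitioner's difference. It can describe whether the whole cluster started high or low. It says nothing about whether the practitioner's patients started worse than the linked controls, and that gap is what disturbs the estimate.
- **Change score.** Subtracting outcome from baseline assumes that each point of baseline gap carries through to follow-up in full. If the true slope is below 1, the gap is over-corrected. A practitioner whose patients happened to start worse than the linked controls then looks somewhat better than he or she is.

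Participant-level ANCOVA, which the protocol uses for its main comparison, avoids both problems. The practitioner analysis gives it up where groups are smallest and chance gaps largest. At stake are the precision of the practitioner estimates and the power to detect real variation between practitioners.

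**Working it through.** **Inputs from the article.** SD 16 points; correlation r = 0.69 (baseline to 3 months); clinically meaningful difference 5 points; 90% power, alpha 5%; 113 per arm.

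**Assumptions.** Equal SDs at baseline and follow-up. The article gives no number of practitioners; 10 to 20 per active arm would mean 113/20 ≈ 6 to 113/10 ≈ 11 analysed participants per side. I use m = 8 per side and show 4 to 20. No 12-month correlation is given.

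**Step 1: the protocol's own figure.** n = 2 × [16 × (1.960 + 1.282)/5]² × (1 − 0.69²) = 215.2 × 0.5239 = 112.7, rounded up to 113. It reproduces with a two-sided alpha, so the trial size already takes the full ANCOVA gain. With change scores the same formula gives 215.2 × 2(1 − 0.69) = 133.4, or 134 per arm.

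**Step 2: the shared cluster mean.** Let the two sides have baseline means a and b from m₁ and m₂ participants with common variance σ². The covariance of the gap (a − b) with the pooled mean is [m₁(σ²/m₁) − m₂(σ²/m₂)]/(m₁ + m₂) = 0, so the pooled mean carries no information on the gap. A simulation agrees (3,000 trials, 15 practitioners, 8 per side, no true practitioner variation). The SD of practitioner differences in raw outcome is 7.85 before adjusting for the cluster mean and 7.83 after. Their correlation with the baseline gap is 0.68 before and 0.66 after.

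**Step 3: the change score.** The variance of a practitioner's difference is k × 2 × 16²/m, with k = 1 for raw outcome, 2(1 − r) = 0.620 for change and 1 − r² = 0.524 for ANCOVA. For outcome minus baseline, the share of the baseline gap carried into the estimate is r − 1 = −0.31. It is +0.69 for raw outcome and 0 for ANCOVA.

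| Per side | SD of baseline gap | Part carried, change | Part carried, raw | SD of estimate: change | ANCOVA | raw |
|---|---|---|---|---|---|---|
| 4 | 11.3 | 3.5 | 7.8 | 8.9 | 8.2 | 11.3 |
| 8 | 8.0 | 2.5 | 5.5 | 6.3 | 5.8 | 8.0 |
| 20 | 5.1 | 1.6 | 3.5 | 4.0 | 3.7 | 5.1 |

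Variance ratio, change to ANCOVA: 0.620/0.524 = 2/(1 + r) = 1.18. Interval width ratio: √1.18 = 1.09.

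**Step 4: both steps together.** In the simulation, adding the cluster mean to the change score moves the SD from 6.15 to 6.13 and the correlation with the gap from −0.39 to −0.37. The combination is a change score in all but name.

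**Step 5: sensitivity.**
- Correlation: the ratio 2/(1 + r) is 1.11 at 0.8, 1.25 at 0.6, 1.33 at 0.5 and 1.43 at 0.4.
- Narrower baseline: suppose the 28% entry limit reduces the baseline SD to about 11, with slope and residual variance unchanged (256 × 0.5239 = 134.1). The change-score excess is then 0.31² × 121/134.1 = 8.7%. A simulation with truncated baselines gave about 8%.
- Cluster mean alone on raw outcome: 1/0.524 = 1.91, a 91% excess. A simulation with 20 practitioners gave about 87%. With the narrower baseline it is 0.69² × 121/134.1 = 43%.

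**Step 6: error rates.** With no true practitioner variation, t-interval coverage was about 95% for raw, change and ANCOVA estimates alike. A 5% heterogeneity test rejected in 4.4% to 5.7% of trials. With an assumed true practitioner SD of 5 points (15 practitioners, 8 per side), power was 47% with ANCOVA, 39% with change scores and 25% with raw outcome. With an assumed SD of 3 points it was 16%, 14% and 10%.

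**The case against.** A reader might infer that chance imbalance will be reported as practitioner differences. The documents do not support that. Chance imbalance is sampling noise, and the planned t-interval for each practitioner already includes it; Step 6 shows no inflation of error rates. Point estimates would mislead only if they were ranked or compared without their intervals, and the article plans an interval for each.

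A reader might also take the 5.5-point carry-over and the excess of about 90% as the size of the problem. Those figures apply only if the cluster-mean adjustment is used alone on raw outcome. The article joins the two steps with *and*, and does not settle whether they are combined or alternative. On the combined reading the effect is modest: an SD of 6.3 against 5.8 at 8 per side. Most of the spread comes from small clusters, and no adjustment removes it.

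The analysis is also exploratory and the text is a summary. A full plan might say how the cluster mean enters the model. If it entered each side's mean separately, the criticism of the shared mean would fall.

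These points reduce the size and the importance of the concern. They do not rescue the sentence as written: the article defines the cluster as holding both sides and names the change score explicitly. At every correlation and baseline spread examined, that method is less precise than participant-level ANCOVA.

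**Conclusion.** The point holds as a minor one about efficiency. On the combined reading, the stated adjustment costs about 18% in variance, or 9% in interval width, relative to participant-level ANCOVA. The variance cost is about 8 to 9% if the entry limit narrows the baseline SD to about 11, and about 33% if the 12-month correlation is 0.5. It also leaves each practitioner's estimate correlated with a chance baseline gap, and lowers the power to detect practitioner variation (39% against 47% in the illustrated case).

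The variance ratio does not depend on cluster size, but the figures in points and the power figures do. The slope of 0.69 rests on equal SDs and on a 3-month pilot correlation used for a trial whose primary endpoint is at 12 months. The simulations treat linked controls as exchangeable with the practitioner's patients apart from any effect. The primary comparison and the sample size are unaffected.

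**What to change.** Replace the baseline sentence with wording such as: *Practitioner effects will be estimated with adjustment for each participant's own baseline NPQ, entered as a covariate with a common slope, as in the primary analysis of covariance.* Drop the cluster-mean and change-score adjustments. This works whether or not the artificial clusters are kept. Practitioner estimates should continue to be shown with their intervals.

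The cost is one sentence of analysis wording. Baseline NPQ is already collected from every participant, so no new data are needed.

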### Treatment/intervention effect modifiers

A treatment/intervention effect modifier is a variable that provides an interaction, such that the effect of X on Y depends on the level of this additional variable. No causal sequence is implied by an interaction. For example, an intervention may be successful for males but not for females. This is called an interaction effect. To explore potential treatment/intervention effect modifiers, we will collect data at baseline on the participants’ age, gender, education and employment, income band, and ethnicity as well as preferences, expectations and beliefs about the interventions. We will also collect preference data at final follow-up to examine if these change post-intervention.

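### The comparison named for testing whether outcome influences later preferences contains no outcome variable, so as worded it shows only whether preferences changed

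*Protocol article*

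**What the plan says.** Three places in the protocol article bear on this.

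- *A summary of the statistical analysis plan*, last sentence. The outcome data are to be looked at "to determine if it influences subsequent preferences by comparing participants’ pre-randomisation preferences to those given at 12 months post-randomisation". The first half of that wording gives the aim, and the second half gives the means.
- *Treatment/intervention effect modifiers*. The second round of preference data has a simpler stated purpose: "We will also collect preference data at final follow-up to examine if these change post-intervention".
- *A summary of the statistical analysis plan*, earlier: "We will use regression models to explore whether preference, belief or expectation are treatment effect modifiers". Here preference is an input and the treatment effect on outcome is the result.

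No other section says that change in preference will be related to change in NPQ or compared between arms.

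**The concern.** Two different questions can be asked of the repeated preference data.

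1. Did preferences change between baseline and 12 months?
2. Given baseline preference and allocated arm, is 12-month preference related to how the participant fared?

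The effect-modifier section asks the first. The closing sentence of the analysis summary asks the second, but the comparison it names answers only the first. Preferences may move because people have become familiar with an intervention, because they did or did not get the arm they wanted, or simply with time. None of these involves outcome. Conversely, if those who improve move towards their allocated intervention and those who do not improve move away, the net change can be close to zero although outcome drives every switch.

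At stake is the interpretation of one exploratory analysis: followed literally, it could credit outcome with drift or overlook a real association.

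**Working it through.** The article gives no figure on this point, so there is none to reproduce. The mismatch follows from the wording, and the arithmetic below only illustrates it.

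**What each analysis uses**

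| Planned item | Variables named | Question it can answer |
|---|---|---|
| Effect-modifier section, repeat preference data | preference at baseline and at final follow-up | did preferences change? |
| Analysis summary, regression models | baseline preference, belief, expectation; outcome | does preference modify the treatment effect? |
| Analysis summary, last sentence | preference before randomisation and at 12 months | did preferences change? (stated aim: does outcome influence preference?) |

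The regression models run from preference to outcome, the reverse of the last sentence's aim, so they do not fill the gap.

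**A worked case.** Take 100 hypothetical participants in one active arm. Assume that 40 prefer the allocated intervention at baseline, 60 do not, and half of each group improve.

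- *Outcome drives every switch.* Of the 30 improved non-preferrers, 20% join: 30 × 0.20 = 6. Of the 20 non-improved preferrers, 30% leave: 20 × 0.30 = 6. Before/after: 40 to 40 − 6 + 6 = 40, no change. By outcome at 12 months: improvers 20 + 6 = 26 of 50 (52%), non-improvers 20 − 6 = 14 of 50 (28%).
- *Outcome irrelevant, general drift.* 15% of non-preferrers join: 60 × 0.15 = 9. 5% of preferrers leave: 40 × 0.05 = 2. Before/after: 40 to 40 + 9 − 2 = 47, a change. By outcome the expected share is the same in improvers and non-improvers: (20 + 4.5 − 1)/50 = 47%.

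The before/after comparison gives the wrong signal in both cases; relating preference to outcome gives the right one.

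**Two simulations.** Sample sizes come from the article: "We will recruit 500 participants in total to the trial", with "in our estimate of sample size we are conservative, allowing for 30% loss to follow-up". That gives 500 × 0.7 = 350 followed up, or 500/3 × 0.7 ≈ 117 per arm. At the 20% loss the article aims for, it is 500/3 × 0.8 ≈ 133 per arm. Everything else is assumed: binary preference, a McNemar test for the before/after comparison, and the switching rates or effect sizes.

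*Set-up 1*: one arm, 1000 runs per scenario, 40% baseline preference. In the drift rows, preferrers leave at a third of the rate shown. In the outcome-driven rows, non-improved preferrers leave at 30% or 45%. The comparator is a logistic model of 12-month preference on NPQ change, adjusted for baseline preference.

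| Scenario | Before/after, n = 117 | Logistic, n = 117 | Before/after, n = 133 | Logistic, n = 133 |
|---|---|---|---|---|
| Drift 15%, outcome irrelevant | 60% | 6% | 63% | 4% |
| Drift 20%, outcome irrelevant | 73% | 5% | 80% | 5% |
| Drift 30%, outcome irrelevant | 90% | 5% | 94% | 7% |
| Outcome drives all switching, 20% join | 3% | 96% | 3% | 97% |
| Outcome drives all switching, 30% join | 3% | 99.8% | 4% | 99.8% |

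*Set-up 2*: N = 350, 2000 runs. Latent preference is a stable part plus noise, each with SD 1. The shift and the effect per SD of outcome change are in those units.

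| Shift | Outcome effect | Before/after rejects | Logistic on outcome rejects |
|---|---|---|---|
| 0 | 0 | 5.4% | 4.5% |
| 0.5 | 0 | 99.7% | 4.5% |
| 0 | 0.5 | 4.9% | 100% |
| 0 | 1.0 | 4.4% | 100% |
| 0.5 | 0.5 | 98.9% | 100% |

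The pattern is the same in both: the before/after comparison responds to net change in preference and not to outcome.

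**The case against.** **The sentence opens with the outcome data.** Its subject is the examination of outcome data, so the authors may mean to derive each participant's change in preference and then relate it to outcome. This is a fair reading and it softens the point. It does not remove it: the clause that gives the means names no outcome variable, and no other section supplies the link.

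**Model detail belongs in the full analysis plan.** The article gives only a summary, and the full plan, if there is one, is not shown. The choice of test, coding and contrast can properly be left to it, and their absence is no fault. What stands is narrower: a comparison is stated, and it does not match its question.

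**The rejection rates are built on assumptions.** This stands in full. The article does not mention a McNemar test or a binary preference. In the first set-up the cancellation is built in, since with equal proportions improving 0.6 × 0.20 = 0.4 × 0.30 and 0.6 × 0.30 = 0.4 × 0.45. The comparator models had no arm-by-change term, so their power does not describe the model recommended below.

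**A stronger reading is tempting.** A reader might infer that the trial will report any shift in preference as an effect of outcome, that the 60% to 99.7% figures are the plan's false-positive rate, or that the trial cannot answer its question. The documents do not support this. Nothing says that a shift will be attributed to outcome without further analysis, and the article plans to collect both NPQ and preference, the data needed for a suitable analysis.

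**Conclusion.** The point holds as a mismatch between a stated aim and the comparison named for it. Taken literally, the comparison answers whether preferences changed and cannot tell an influence of outcome from drift or the effect of allocation. That conclusion follows from the variables named and needs no assumed figures.

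Its size cannot be fixed from the article. The simulated rates illustrate direction only, under assumed switching rates, binary scoring and a paired test. The analysis is exploratory, and the primary NPQ comparison at 12 months does not depend on it. This is a minor correction of wording and method.

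**What to change.** Reword the last sentence of *A summary of the statistical analysis plan* so that:

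- 12-month preference is regressed on NPQ change from baseline (logistic, or multinomial over the preference categories), adjusted for baseline preference and allocated arm;
- the association may differ by arm, through an arm-by-NPQ-change term, because improvement under one intervention would be expected to shift preference towards that intervention;
- the model is repeated with 6-month NPQ, so that outcome is measured before preference, since 12-month NPQ and preference are collected together;
- the result is reported as an exploratory association and not as proof of influence, because outcome is not randomised.

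Keep the simple before/after comparison for the question in *Treatment/intervention effect modifiers*, which it answers.

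The cost is one reworded sentence and an extra regression, run at two outcome times, on data already planned: NPQ at baseline, 6 and 12 months, and preference at baseline and final follow-up. The model has more parameters than a paired comparison, so estimates will be somewhat less precise. Participants, visits and questionnaires are unaffected.
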